### Other patient-related outcome measures

Both groups will complete PROMs over four timepoints (see figure 1, table 1). The questionnaires are as follows:

STAI, DASS21 and PedsQL 4.0 for all patientsPAC-QoL (including cough severity scores) for patients with a cough

PedsQL 4.0 is a validated, generic assessment instrument that assesses the child’s and parent’s perceptions of health-related QoL.^23 33^ It has generic core scales (physical, emotional, social and school) and a total score, normalised to provide a maximum score of 100. There are separate questionnaires according to the age of the child (ages 1–12 months, 13–24 months, 2–4 years, 5–7 years, 8–12 years and 13–18 years). PedsQL 4.0 has been previously used to examine the burden of disease in chronic cough.^34 35^ PAC-QoL is a validated outcome measure to assess QoL related to childhood acute cough.^26^ There are 16 questions pertaining to cough. It has been used to examine the burden of disease in acute cough.^36^ A cough severity score^27^ is also performed along with the PAC-QoL. This score has three questions about the severity and the quality of the cough. The PAC-QoL is correlated with the cough severity scores.^26^ DASS21^24^ is a validated self-report instrument to measure the parent’s depression, anxiety and stress. STAI is a validated assessment instrument to measure anxiety in adults.^25^ There are two sets of 20 questions with one set of questions addressing the state of anxiety and the other set of questions addressing the trait of anxiety.

Each participant completes the study 6 months after the date of recruitment, after all information have been collected. All the data are documented on paper-based case report forms using standardise data collection sheets.

### Exit criteria during the study

Exit criteria are defined as:

If the physician decides that urgent FB is required and cannot wait on the elective listIf consent is withdrawn by parentIf there is any severe FB-related adverse event that precludes from the FB being completed

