**Methods and analysis:**

Our parallel single-centre, single-blind RCT (commenced in May 2020) has a planned sample size of 114 children (aged <18 years) recruited from respiratory clinics at Queensland Children’s Hospital, Brisbane, Australia. Children are randomised (1:1 concealed allocation) within two strata: age (≤2 vs >2 years) and indication for FB (chronic cough vs other indications) to either (a) early arm (intervention where FB undertaken within 2 weeks) or (b) delayed (control, FB undertaken at usual wait time). Our primary outcome is the difference between groups in their change in QoL at the T2 timepoint when the intervention group has had the FB and the control group has not. Our secondary outcomes are change in management, change in PROMs, adverse events and the Likert scales.

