### Randomisation and allocation

Randomisation is stratified by as follows: (a) indication for FB (chronic cough or other indications (recurrent stridor, recurrent wheeze, haemoptysis, recurrent pneumonia, persistent radiographic changes, suspicion of foreign body, unexplained dyspnoea and others) and (b) age (≤2 or >2 years). The computer-generated permuted block (block size 4–6) randomisation allocation sequence (1:1 ratio) was prepared by an independent person not involved in the study. After informed consent, children are randomised to one of the two arms: (1) intervention group where the FB occurs early or (2) control group where the FB occurs within the normal waiting time. Parents of participants will not be informed of the usual wait times; thus, they are unaware of whether they are in early or ‘usual-wait’ group and hence will remain blinded. Blinding the physician is not possible.

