### Overview of procedures for intervention and control groups

The outline of study procedures for both control and intervention groups is summarised in figure 1 and table 1. At enrolment (timepoint 1 (T1), baseline), both groups complete the various PROM questionnaires, that is, STAI, DASS21 and PedsQL 4.0. PAC-QoL (including cough severity scores) is also completed if chronic/recurrent cough is the indication for FB. All the PROM questionnaires are filled out by the parents/guardians. Children aged ≥5 years also complete a PedsQL 4.0 questionnaire. The intervention group (early-group) has their FB undertaken within 1–2 weeks of enrolment (followed by a phone call 48–72 hours after). At timepoint 2 (T2), children in the intervention group are seen in a follow-up clinic 2–3 weeks after their FB, and their parents repeat the PROM questionnaires, while the control group also repeat the PROM questionnaires (prior to their FB, ie the control group has not had their intervention yet at this timepoint) (see figure 1, table 1). At timepoint 3 (T3), the control group has their FB (followed by a phone call 48–72 hours after) and is clinically reviewed in a clinic within 2–3 weeks. Further PROMs are collected in both groups at timepoint 4 (T4), which is 12 weeks after baseline, and 24 weeks (6 months) after baseline as the final timepoint 5 (T5). All children receive the same standard of care.

**Table 1 T1:** Outline of study procedures

Procedure undertaken	T1 (Baseline)	T1+1–2 weeks	T2 (T1+4–5 weeks)	T3 (T1+≥6 weeks)	T3+2–3 weeks	T4 (T1+12 weeks)	T5 (T1+24 weeks)
Screening for eligibility	**√ ∞**						
Informed consent	**√ ∞**						
Randomisation	**√ ∞**						
Medical history	**√ ∞**						
Medical chart review	**√ ∞**		**√ ∞**		**∞**		
Clinical assessment	**√ ∞**		**√**		**∞**		
PedsQL 4.0	**√ ∞**		**√ ∞**			**√ ∞**	**√ ∞**
DASS21	**√ ∞**		**√ ∞**			**√ ∞**	**√ ∞**
STAI QoL	**√ ∞**		**√ ∞**			**√ ∞**	**√ ∞**
PAC-QoL (if cough present)	**√ ∞**		**√ ∞**			**√ ∞**	**√ ∞**
Cough severity score (if cough present)	**√ ∞**		**√ ∞**		**∞**	**√ ∞**	**√ ∞**
Spirometry if able	**√ ∞**		**√**		**∞**		
FB		**√**		**∞**			
Post-FB phone call (48–72 hours post-FB)		**√**		**∞**			
BAL result review			**√**		**∞**		
Physician opinion on diagnosis and management	**√ ∞**	**√**	**√**	**∞**	**∞**		

^√^ = Early bronchoscopy group (intervention)

^∞^ = Normal-wait bronchoscopy group (control)

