### Sample size

Our target sample size is based on finding a difference between groups of at least the minimal clinically important difference (MCID) of PedsQL 4.0 (primary outcome). With MCID of the total parent proxy of 4.5 (SD 8.25),^40^ for a study power of 90% (α=0.05), data from 48 children per group (total 96) are required. To account for a dropout of 15%, we will enrol a total of 114 children (57 children per group). For the secondary outcome of ‘change in management’, the effect size is conservatively estimated based on pilot data of a random selection of 20 FBs and using the a priori definitions aforementioned. Our pilot work found that FB led to a change in management in 14 of the 20 children (70%). The sample size of 114 provides 95% power (α=0.05) for this outcome (taking into account 15% loss).

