### Data management and statistical analyses and reporting

Essential study documentation and management of all study files are in accordance with good clinical practice guidelines. Further information about data management are provided in online supplemental file 1.

Data will be reported in accordance with Consolidated Standards of Reporting Trials, and ‘intention to treat’ (ITT) analyses will be used. For PedsQL 4.0, data will not be imputed, and ITT will consist of ‘available cases’. Based on our previous RCT,^38^ the change in PedQL 4.0 is expected to be normally distributed. The difference (with 95% CI) between groups of the change in QoL will be calculated using unpaired Student’s t-test. If the groups are imbalanced at baseline, regression analyses (adjusting for baseline factors) will be used instead. For the secondary outcomes of DASS21, STAI and PAC-QoL (including cough severity scores), the same method as per PedsQL 4.0 will be used. For the outcome of ‘change in management’, χ^2^ will be used to analyse the difference in the proportion between groups, presented as odds ratio (95% CI). Likert scales regarding opinions towards benefit of FB (parent and doctor perspective) will be reported as mean (SD) or median (25th–75th percentile), based on data distribution.

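### Two exit criteria are post-randomisation events linked to arm, and with ITT defined as unimputed available cases they may remove different children from each arm before T2

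*Protocol article*

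**What the plan says.** The section on exit criteria names three reasons for exit and does not distinguish their consequences: a physician's decision that FB has become urgent, withdrawal of consent by the parent, and "any severe FB-related adverse event that precludes from the FB being completed". It does not say whether questionnaires continue after an exit.

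The statistical section promises intention-to-treat analysis and then defines it for the primary outcome: "For PedsQL 4.0, data will not be imputed, and ITT will consist of ‘available cases". The primary endpoint is the T1–T2 change in PedsQL 4.0, so a child without a T2 score contributes nothing to it.

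On timing, the overview of procedures states: "The intervention group (early-group) has their FB undertaken within 1–2 weeks of enrolment". Table 1 places T2 at 4–5 weeks and the control arm's FB at T3, 6 weeks or more after baseline. At T2, "the control group has not had their intervention yet at this timepoint". The randomisation section adds: "Blinding the physician is not possible".

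**The concern.** Randomisation makes the arms comparable only if children are kept in the comparison whatever happens to them afterwards. Two of the three exits are things that happen afterwards, are tied to how the child is doing, and have different chances of occurring in the two arms because FB is scheduled at different times. One removes early-arm children whose procedure went badly. The other removes mainly control children who got worse while waiting. Those courses are part of what the trial sets out to compare.

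If exit means no T2 questionnaire, the available-case analysis compares selected subsets of the randomised groups. The urgent-FB rule carries a further weakness: the physician who decides may know the arm, so an unblinded judgement can determine who enters the primary analysis. The 15% dropout allowance protects the number of children analysed. It does not protect comparability.

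**Working it through.** **Inputs from the protocol article.** Enrolment is 57 per arm, MCID 4.5 points and SD 8.25 (Sample size). Early FB is at 1–2 weeks, T2 at 4–5 weeks and control FB at 6 weeks or later (Overview of procedures, Table 1). The article gives no expected number of exits and no outcomes for exiting children, so both are assumed below.

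**The plan's own figure.** The dropout step reproduces: 48 / 0.85 = 56.5, rounded up to 57 per arm and 114 in total. (The 48 itself does not follow from 4.5 and 8.25 at 90% power; that is a separate matter. Here 8.25 serves only as a yardstick.)

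**Step 1: adverse-event exit before T2.** Only early-arm children have a scheduled FB before T2. A control child who has urgent FB in that window has already met the urgent-FB criterion. By design this exit can therefore arise only in the early arm.

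**Step 2: urgent-FB exit before T2.** A child can meet this criterion only while waiting. Before T2 that is 1–2 weeks in the early arm and 4–5 weeks in control. Under a constant hazard, the control share is control weeks / (control weeks + early weeks):
- lowest: 4 / (4 + 2) = 67%, a ratio of 2:1
- highest: 5 / (5 + 1) = 83%, a ratio of 5:1

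The share could be higher if an early slot makes an urgent procedure less necessary, but the documents give no figure for that. Control waiting after T2 has no bearing on the primary endpoint.

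**Step 3: effect of each lost child.** If k of 57 children in an arm are lost, and their mean change is D points worse than that of the children who remain, the available-case mean exceeds the full-arm mean by (k / 57) × D. Take D as 1 SD (8.25) or 2 SD (16.5):

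| Children lost in one arm | D = 8.25 | D = 16.5 |
|---|---|---|
| 1 (1.8%) | 0.14 | 0.29 |
| 2 (3.5%) | 0.29 | 0.58 |
| 4 (7.0%) | 0.58 | 1.16 |
| 6 (10.5%) | 0.87 | 1.74 |

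As a share of the MCID, 1.16 / 4.5 = 26%.

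**Step 4: direction and net effect.** The bias in the early-minus-control difference is (k_E / 57) × D_E − (k_C / 57) × D_C. Early-arm losses favour early FB; control losses favour waiting. Equal losses with equal deficits cancel. With 1 early and 4 control losses, all at 16.5, the net is (1 − 4) / 57 × 16.5 = −0.87 points. At a deficit of 16.5, a net bias of 1 point needs 1 / 16.5 = 6.1% of an arm, which means at least 4 more children lost in one arm than in the other. At 8.25 it needs 1 / 8.25 = 12.1%, or at least 7.

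**The case against.** The strongest reply is that the decisive step is not written down. The article lists exit criteria; it does not say that questionnaires stop or that the child leaves the analysis. It is a condensed account that refers to a supplement for data management and safety monitoring, and the full protocol may say that follow-up continues. This stands as a limit on certainty. Against it, exit is listed beside withdrawal of consent with no distinction, so the text as it stands permits the loss.

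Three stronger readings are tempting, and the documents do not support them.
- A reader might infer that both exits occur almost exclusively in one arm. That is right for the adverse-event exit. For urgent FB the schedule supports only mostly control, at 67–83%.
- A reader might infer that the adverse-event outcome itself loses data. It is not shown to. Complications during FB are recorded at the procedure, and a phone call follows at 48–72 hours. What may be lost is the T2 questionnaire of such a child.
- A reader might call the plan self-contradictory on intention to treat. It openly defines its set as available cases. The weakness is that this definition, joined to these exits, does not deliver a comparison of the groups as randomised.

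It is also fair that few exits are likely. Children needing urgent FB are excluded at entry, and the adverse-event rule requires an event that is both severe and stops the procedure. Six losses in one arm would be about 70% of the whole 15% allowance (10.5 / 15). Finally, analysing controls who had urgent FB as randomised is a choice of comparison that should be stated openly.

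**Conclusion.** The concern holds in a limited form. Two exit criteria are post-randomisation, prognosis-linked and unequal between arms before T2, and one depends on an unblinded decision. If exit ends questionnaire collection, which is the natural but unstated reading, the available-case comparison loses different children from each arm.

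The size cannot be fixed from the documents. It rests on assumed exit counts and deficits, at about 0.14 to 0.29 points per lost child, and the two exits pull in opposite directions. With few exits the net bias is probably under 1 point. That is unlikely to create or hide an effect of the planned 4.5 points alone, but cancellation cannot be relied on because nothing suggests equal rates or equal deficits. If the full protocol already continues follow-up after these events, a sentence saying so settles the matter.

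**What to change.** - Make withdrawal of consent the only reason to stop data collection. A child who meets either of the other two criteria leaves the procedure timetable but stays in the trial and completes the T2, T4 and T5 questionnaires.
- Analyse these children in their randomised arm, and state that this is a treatment-policy comparison.
- Report the number of urgent-FB and incomplete-FB events by arm, with the reason.
- Where T2 data were not collected from children who have already exited, add a sensitivity analysis for the missing values over a stated range of deficits, by arm.

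Clinical care does not change. The cost is a short protocol clarification, questionnaires for a handful of children and one extra analysis. The comparison is slightly diluted by control children who had urgent FB before T2. The article expected recruitment to finish by late 2023 and follow-up by mid-2024, so T2 scores already missed cannot be recovered. For those children, reporting by arm and the sensitivity analysis are what remains.

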### Endpoints

The primary endpoint is a change in QoL determined by the PedsQL 4.0 between the two arms at T2 (figure 1) (prior to control group having their FB) and the baseline (T1). The secondary endpoints are as follows: (a) proportion of children whereby FB changes clinical management based on a priori factors, (b) change in DASS21 scores (T2 minus T1), (c) change in PAC-QoL scores (including cough severity scores) (T2 minus T1), (d) change in STAI scores (T2 minus T1), (e) Likert scores reflecting opinions relating to the benefit of FB (patient and doctor perspective) in clinical practice and (f) change in PedsQL 4.0, DASS21, PAC-QoL (including cough severity score) or STAI in T4 and/or T5 (to examine if there is any sustained effect by the intervention (FB)).

A priori definitions of change in management are as follows:

Decision to admit for intravenous antibiotics and physiotherapy directly after FB. This will be based on the secretion score^29^ and the secretion colour which is part of a validated FB bronchitis score (Bscore)^37^ (see figure 2 for details of the management pathway). The importance of this management strategy in improving clinical outcomes has been previously highlighted by research findings.^38 39^
Started oral (PO) antibiotics directly after FB (excluding azithromycin for CT scan-proven BE). This will also be based on the secretion score,^29^ which is part of the Bscore^37^ (see figure 2 for details of the management pathway).Change in type of intravenous or PO antibiotics (or change from oral to intravenous) after BAL culture results are available(eg, anti-pseudomonal antibiotics for *Pseudomonas aeruginosa*).Referred to another specialty for appropriate management changes for intervention based on findings on FB. Examples include referral to surgeons such as cardiothoracic (eg, for vascular ring), ENT (eg, subglottic lesion) and paediatric (eg, tracheo-oesophageal fistula) surgeon.

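### Endpoint (f): after controls have bronchoscopy at T3, the T4 and T5 comparisons contrast early with usual-wait bronchoscopy and cannot measure a sustained effect of the procedure

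*Protocol article*

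**What the plan says.** The Endpoints section lists as secondary endpoint (f) the change in PedsQL 4.0, DASS21, PAC-QoL with cough severity, or STAI at T4 and/or T5. Its stated purpose is "to examine if there is any sustained effect by the intervention (FB").

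The section on procedures for the two groups and Table 1 fix the schedule:

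- Early arm: "has their FB undertaken within 1–2 weeks of enrolment".
- T2 (T1 + 4–5 weeks): "the control group has not had their intervention yet at this timepoint".
- Controls: "At timepoint 3 (T3), the control group has their FB". Table 1 puts T3 at 6 weeks or more after T1, with no upper limit.
- Later visits: "timepoint 4 (T4), which is 12 weeks after baseline, and 24 weeks (6 months) after baseline as the final timepoint 5 (T5").
- Both arms: "All children receive the same standard of care".

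The statistical section gives one approach. "The difference (with 95% CI) between groups of the change in QoL will be calculated using unpaired Student’s t-test", replaced by regression if the arms are imbalanced at baseline. For DASS21, STAI and PAC-QoL, "the same method as per PedsQL 4.0 will be used". Both versions compare the arms with each other.

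**The concern.** A sustained effect of bronchoscopy is a contrast between having had it and not having had it, followed over time. The design provides that contrast at T2 and withdraws it at T3. The protocol respects this for the primary endpoint, which it places before the control procedure, but endpoint (f) keeps the language of an effect of bronchoscopy after the comparator has gone.

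What is at stake is interpretation. A T4 or T5 difference near zero could be taken to mean that the T2 benefit wore off, when the same result is expected if the benefit is permanent and controls have caught up. The Discussion expects the results to inform hospital policy and guidelines, so the meaning of these later comparisons should be settled before they are reported.

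**Working it through.** **Inputs.** Benefit 4.5 points, SD 8.25, α = 0.05 and 48 evaluable children per group (Sample size section); visit times as listed above. Assumptions: the test is two-sided, and 8.25 is the SD of change in each arm.

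**The plan's own figure.** The plan gives no figure for T4 or T5. Its only one is 48 per group for the primary outcome at 90% power. The usual formula gives n = 2 × (1.960 + 1.282)² × 8.25² / 4.5² ≈ 71 per group, and 48 per group gives about 76% power, so 48 is not reproduced. That is a separate matter. It affects only the non-zero rows in the table below; a true difference of 0 is rejected with probability 0.05 whatever the sample size or SD.

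**Step 1: who has had bronchoscopy, and how long ago.**

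| Visit | Early arm, weeks since procedure | Control arm, weeks since procedure |
|---|---|---|
| T2 (4–5 weeks) | 2–3 (follow-up clinic) | not yet done |
| T4 (12 weeks) | 12 − 2 = 10 to 12 − 1 = 11 | at most 12 − 6 = 6 |
| T5 (24 weeks) | 24 − 2 = 22 to 24 − 1 = 23 | at most 24 − 6 = 18 |

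**Step 2: what the between-group difference estimates.** Let r be the share of the 4.5-point benefit present in the early arm at a visit, and c the average share present in controls. Randomisation balances natural recovery and other care on average, so

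expected difference D = 4.5 × (r − c).

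At T2 controls have not had the procedure, so c = 0 and D = 4.5r: the comparison measures the effect. At T4 and T5, c is unknown and D fixes only r − c. Durability is a question about r.

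**Step 3: numbers.** Standard error = 8.25 × √(2/48) = 1.684. Rejection probability = Φ(D/1.684 − 1.960) + Φ(−D/1.684 − 1.960).

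| Pattern at the visit | r | c | D | P(reject) |
|---|---|---|---|---|
| Fully kept in both arms | 1 | 1 | 0 | 0.05 |
| Half present in both | 0.5 | 0.5 | 0 | 0.05 |
| None in either | 0 | 0 | 0 | 0.05 |
| Kept early, controls at three quarters | 1 | 0.75 | 1.125 | 0.10 |
| Kept early, controls at half | 1 | 0.5 | 2.25 | 0.27 |
| Half faded early, fresh in controls | 0.5 | 1 | −2.25 | 0.27 |
| Lost early, fresh in controls | 0 | 1 | −4.5 | 0.76 |

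The first three rows are opposite answers to the durability question and give the same expected result.

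**Step 4: controls still waiting at T4.** If a share w of controls has not had the procedure by 12 weeks and the benefit is permanent, then c = 1 − w and D = 4.5w. The protocol gives no wait-time distribution, so w is an assumption: w = 0 gives 0, w = 0.2 gives 0.9, and w = 0.5 gives 2.25.

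**The case against.** **Endpoint (f) does not say that it is a between-group comparison.** This is true, and the sentence extending the PedsQL method to the other scales names no visit. Change within each arm from T1 is a possible reading. It would describe persistence, but it has no control for natural recovery, regression to the mean or other care, so it could not attribute persistence to bronchoscopy either. The stated purpose is unsupported on both readings.

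**The design limit is acknowledged.** The primary endpoint and endpoints (b) to (d) sit at T2, and the Discussion names the waitlist design as the first limitation. This protects the main inference. But the Discussion says only that withholding access is not ethically possible. It does not say that the contrast ends at T3, and the purpose of (f) stands.

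**Analysis detail may be in a plan not shown.** That could settle the method, but no later analysis restores a bronchoscopy-free comparator. The fault is the stated purpose, not an omitted detail.

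**T4 and T5 are not uninformative.** This stands. A reader might infer that lasting and vanished benefit always both give a difference near zero. That holds only when the two arms carry equal benefit at the visit. The early arm is 10–11 weeks from the procedure at T4 and treated controls at most 6, so benefit that fades over that interval would favour control. If bronchoscopy does no net harm in controls (c ≥ 0), a positive difference would indicate that some early benefit remains.

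**Few controls may be waiting at T4.** A reader might infer from the missing upper limit on T3 that many are. The documents do not support this: Table 1 places the control procedure and its review before T4.

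**Conclusion.** The point holds as a mismatch between the stated purpose of endpoint (f) and what the design can estimate after T3. The T4 and T5 comparisons estimate early versus usual-wait bronchoscopy. That is a legitimate question about whether the delay has a lasting cost, but not the one stated.

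The key assumption is that controls gain about the same benefit from their own procedure, which follows from the trial's hypothesis but is not established. Under it, full, equally reduced and absent benefit all have expected difference 0 and rejection probability 0.05. Without it, the difference ranges in the scenarios shown from −4.5 to +2.25 points and still reflects r − c rather than r. A negative T4 difference is therefore no cleaner a measure of durability than a null. Any controls still waiting would blur T4 further, by an amount the document does not allow one to calculate.

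The protocol nowhere commits to reading a T4 or T5 null as lost benefit, so that misreading is a foreseeable risk, not a stated plan. The primary endpoint, the T2 secondary endpoints and the sample size are unaffected. The correction is worth making because it changes what the trial may conclude about durability.

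**What to change.** 1. Rename endpoint (f) as early versus usual-wait bronchoscopy at 12 and 24 weeks, and delete the sustained-effect purpose.
2. State that no bronchoscopy-free control remains after T3, so a T4 or T5 null is not evidence against a lasting benefit, and that a difference favouring control does not by itself measure loss of benefit.
3. Report the early arm's change from T1 and from T2 to T4 and T5, with 95% confidence intervals, labelled descriptive and uncontrolled.
4. Report the number of controls who had not had bronchoscopy by T4, from the recorded procedure dates, so that the T4 contrast can be read for what it is.

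A mixed model with bronchoscopy status and time since the procedure as time-varying terms is not needed. After crossover it would rest on the modest timing gap between the arms and on non-randomised variation in control waiting time. At most it is exploratory.

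The cost is a change of wording and simple summaries of data already scheduled for collection. What is given up is a claim that the design cannot support.
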